###### *Exploratory Endpoints:*

1. Number of partial or full IMP doses of PCC and FP administered during the first 24 hours after the start of surgery.
2. Incidence of major bleeding, using the validated e-CABG and universal definition of perioperative bleeding (UDPB) in cardiac surgery (1, 72) scores and their individual components during the first 24 hours after start of surgery, as well as a modified version of the UDPB not including PCC and FP requirements.
3. Amount of allogeneic blood products (for each type of product and cumulatively) from start of surgery to postoperative day (POD)-7.
4. Number of patients who do not receive any RBC transfusions or any allogeneic blood transfusions from start of surgery to POD-7.
5. Number of patients receiving recombinant activated factor VII (rFVIIa) during the first 24 hours after the start of surgery
6. Number of patients receiving fibrinogen concentrate during the first 24 hours after the start of surgery.
7. Change in coagulation parameters (INR, ROTEM [EXTEM CT and MCF] and fibrinogen levels) within 75 minutes before and after IMP administration, where performed as part of standard of care.
8. Time elapsed from first IMP administration to time leaving the operating room.

### 3.1.2 Safety Endpoints

All AEs and SAEs will be collected from beginning of surgery (defined as entry into OR) to POD-28.

SAEs will be collected individually and as a composite (death, myocardial infarction, stroke, acute liver injury, acute kidney injury and thromboembolic events).

Incidence of all transfusion reactions, including transfusion-associated circulatory overload (TACO) and transfusion-related acute lung injury (TRALI) as per the International Society of Blood Transfusion (ISBT) (16) imputability of 'possible' or higher will be compared.

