Our results are similar to those from other studies. A recent systematic review only identified 4 small, non-randomized studies – including our own (59) – comparing perioperative PCCs to FP in cardiac surgery (60). The meta-analysis showed PCCs were associated with reduced risk of RBC transfusion (OR 2.22; 95%CI 1.45-3.40) and fewer units of RBCs transfused (OR 1.34; 95%CI 0.78-1.90). PCCs were not associated with increased hospital mortality (OR 0.94; 95%CI 0.59-1.49), stroke (OR 0.80; 95%CI 0.41-1.56) or AKI occurrence (OR 0.80; 95%CI 0.58-1.12), suggesting that PCCs are more effective than FP without decreasing safety. In one of the studies in the systematic review, Arnekian and colleagues (61) compared three groups of cardiac surgical patients: 24 who received only PCC, 26 who received only FP, and 27 who received both products. In an unadjusted analysis, they found that RBC transfusions occurred least frequently in the PCC group and most frequently in patients who received both products. However, given the small sample size and lack of risk-adjusted analysis, few conclusions can be drawn from this study. In another study that included only patients who underwent pulmonary endarterectomy with cardiopulmonary bypass (CPB), Ortmann and colleagues (62) compared transfusion requirements and outcomes between 55 patients who received only FP and 45 patients who received only PCC for management of post-CPB coagulopathic bleeding. In an unadjusted analysis, they found that the PCC group had lower blood loss than the FP group, but transfusion rates were similar. They conducted multivariable regression analysis for AEs and found no differences between the two groups. However, given its small sample size, limited generalizability, and lack of risk-adjustment for efficacy outcomes, this study should be interpreted with caution. In a larger study, Cappabianca and colleagues (63) used propensity scores to match 225 patients who received PCC (with or without FP) to 225 patients who received only FP for management of post-CPB coagulopathy. They found that RBC transfusion requirements were lower in the PCC group (84% versus 93%), as were multiple (more than two units) RBC transfusions (51% versus 70%) and number of units of RBCs transfused (3.4 versus 5.2 units). While there were no major between-group differences in adverse outcomes, in a regression analysis that incorporated the propensity score the authors noted an association between PCC use and acute kidney injury that led them to caution about this potential risk. Similarly, in a recent multi-centre observational study not included in the above systematic

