
review, Biancari and colleagues compared 101 patients who received FP following coronary artery bypass grafting to 101 propensity-score-matched patients who received PCC with or without FP (64). PCC was associated with a significant decrease in rate of RBC transfusions (67.3% vs. 83.2%), but was also associated with an increased risk of acute kidney injury. However, there were many limitations to this study, including unknown differences in PCC dosage, bleeding severity and coagulopathy. Furthermore, in the group of patients that received both FP and PCC, it was not known what the order of administration was and so PCC could have been given as salvage therapy (64). Together, these studies suggest that PCC may be more efficacious than FP in cardiac surgery; however, data from well-designed, prospective, randomized trials are lacking.

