### 6.1.3 Visit 2: Postoperative days 2-7 (or at discharge if earlier)

- Collect daily laboratory assessments where available as part of routine care
  - Chemistry (sodium, potassium, chloride, bicarbonate, pH)
  - Hematology (complete blood count)
  - Coagulation profile
  - Safety labs (creatinine, liver function tests [AST, ALT], bilirubin, troponin)
- Collect transfusion requirements
- Collect extubation time (if applicable)
- Collect length of stay in the ICU and hospital (if applicable)
- Collect AEs and SAEs

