#### 4.7.2 Laboratory variables

In case of derived items in the database (e.g. after transformation to standard units, see DMP), only the derived items will be analyzed. Results of all individual lab tests will be listed in original and standard units in appendix 16.2 to the clinical trial report.

The following laboratory parameter will be analyzed (as available from local labs):

|                     |                                                                                        |
|---------------------|----------------------------------------------------------------------------------------|
| Coagulation profile | PT, PTT, INR, fibrinogen activity via Clauss assay,
ROTEM EXTEM CT, ROTEM EXTEM MCF |
| Hematology          | Standard panel as per local lab                                                        |
| Clinical chemistry  | Standard panel as per local lab                                                        |
| Safety labs         | Troponin, ALT/ALP, Bilirubin, Creatinine                                               |

All laboratory values will be classified as normal or abnormal according to the laboratories' reference ranges and indicated as clinically significant or not clinically significant by the investigator on specified ranges. The following approaches will be taken for each laboratory parameter for the statistical analysis:

Quantitative data will be examined for trends using descriptive analysis (number of patients, number of missing values, mean, SD, median, quartiles, minimum, maximum) of actual values at each scheduled time point and changes from baseline to each scheduled time point. In addition mean concentration vs. time profiles (including standard deviations) will be plotted by treatment to illustrate any time trends.

Qualitative data based on reference ranges will be described according to the categories (i.e., low, normal, high).

Shift tables illustrating changes with respect to the laboratories' reference ranges between baseline and a defined scheduled time point.

Patient listings will be provided showing individual lab abnormalities.

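### Acute kidney injury has no creatinine-based definition: its incidence rests on reported events, and no planned display counts patients with a stated rise from baseline

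*Combined protocol and SAP*

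**What the plan says.** **Endpoint.** Protocol 3.1.2, repeated in SAP 4.7: "SAEs will be collected individually and as a composite (death, myocardial infarction, stroke, acute liver injury, acute kidney injury and thromboembolic events". SAP 4.7.1 also lists AKI among the special cases of treatment-emergent events, and any AKI report falls into the tables by system organ class and preferred term. A MedDRA query is specified only for thromboembolic events. No creatinine criterion, term set or adjudication is given for AKI.

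**From laboratory value to event.** Protocol 7.3.5 leaves clinical significance to the investigator; abnormalities judged significant become AEs or SAEs. Protocol 7.4.3 says that SAEs expected from the nature of the surgery are not treated as SAEs, and does not name them.

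**Data.** Creatinine is a safety laboratory test at Visit 1 and at Visit 2. For Visit 2, Protocol 6.1.3 says: "Collect daily laboratory assessments where available as part of routine care". That visit ends at discharge if discharge comes before day 7.

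**Planned displays.** SAP 4.7.2: "Qualitative data based on reference ranges will be described according to the categories (i.e., low, normal, high"), with shift tables from baseline, summary statistics of values and of changes from baseline, mean profiles by treatment, and listings of abnormalities. Protocol 9.2.1 adds scatterplots and a count of patients with clinically significant values.

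**Prior evidence (Protocol 1.1).** AKI is named beside thrombotic events and disseminated intravascular coagulation as a possible PCC risk. In one matched cohort, "the authors noted an association between PCC use and acute kidney injury"; in another, PCC "was also associated with an increased risk of acute kidney injury". The meta-analysis reports "AKI occurrence (OR 0.80; 95%CI 0.58-1.12), suggesting that PCCs are more effective than FP without decreasing safety".

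**The concern.** Protocol 1.2 gives the pilot two tasks that need a dependable AKI rate: comparing safety data for early signals and supplying inputs for Phase 3. The evidence on AKI is mixed, which is a reason to measure it in the same way for every patient. As planned, two patients with the same creatinine course can be counted differently. One site may report an event and another may not, and a serious event may be regarded as expected after cardiac surgery and so leave both the SAE count and the composite. Serial creatinine, which could supply a uniform rule, is already in the database but is not turned into a patient-level outcome.

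**Working it through.** The documents state no AKI rate, effect size or power, so there is no figure to reproduce. Every rate, limit and distribution below is an assumption. The only input from the plan is 50 evaluable patients per arm (Protocol 9.1).

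**1. Does any planned output give the incidence of a stated rise from baseline?**

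| Planned output | Patient-level count? | Why it does not give this incidence |
|---|---|---|
| AE and SAE tables, special-cases listing, composite | Yes | Depends on reporting; no criterion |
| Clinically significant values | Yes | Investigator judgement; neither document gives the ranges |
| Low/normal/high categories, shift tables | Yes | Tied to the reference range, not to the patient's own baseline |
| Changes from baseline (mean to maximum), mean profiles | No | Group summaries; the maximum shows one extreme only |
| Scatterplots, abnormality listings | No | Visual or line data; no rule applied |

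**2. What does a shift table miss?** Take a 1.5-fold rise as an illustration. It stays within normal whenever baseline is at most ULN/1.5 (ULN = upper limit of normal): 90/1.5 = 60, 105/1.5 = 70, 120/1.5 = 80 umol/L. With ULN 105:

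- 70 to 105 stays normal (missed).
- 80 to 120 moves from normal to high (caught).
- 95 to 142.5 moves from normal to high (caught).
- 110 to 165 stays high (missed).
- 150 to 225 stays high (missed).

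A simulation used lognormal baselines (median 75, 90 or 105; log-SD 0.30), a lognormal ratio of peak to baseline (median 1.15; log-SD 0.30) and ULN 90, 105 or 120. About 19% of patients reach a ratio of 1.5. A normal-to-high shift catches 29% to 63% of them, with specificity 0.85 to 0.92. Of patients who shift, 40% to 61% meet the ratio rule. The simulation uses the peak value. The planned table uses a defined scheduled time point, which need not be the day of the peak.

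**3. What would incomplete reporting do?** Assume control risk p, odds ratio 2 and n = 50 per arm, with q = 2p/(1 + p). The 95% CI for the risk ratio runs from the estimate divided by F to the estimate times F, where F = exp(1.96 x sqrt[(1-q)/(50q) + (1-p)/(50p)]). If half the cases in each arm are reported, p and q are halved.

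| p | q | Power, all / half reported | F, all / half reported |
|---|---|---|---|
| 10% | 18.2% | 0.21 / 0.12 | 2.77 / 4.45 |
| 20% | 33.3% | 0.32 / 0.16 | 1.97 / 2.82 |
| 30% | 46.2% | 0.38 / 0.17 | 1.68 / 2.30 |

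For p = 20% the true risk difference is 33.3 - 20.0 = 13.3 points; half-reporting gives 16.7 - 10.0 = 6.7 points. Power is low throughout.

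**4. Does a more frequent outcome tighten the interval?** Compare 6% with 25% control risk, odds ratio 2 in both, so PCC risks are 11.3% and 40%.

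- Log odds ratio: SE = 0.744 and 0.436, a ratio of 0.59. The interval is about 41% narrower at the higher rate.
- Risk difference: half-width 1.96 x sqrt[p(1-p)/50 + q(1-q)/50] = 11.0 and 18.1 points. The interval is wider at the higher rate.

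**The case against.** **The plan is not blind to AKI.** A reader might infer that the planned displays cannot detect it. That goes too far. Shift tables catch some rises, a large rise would show in the maximum change or the scatterplots, and significant values are counted and documented as AEs. This stands, and it limits the point to the missing per-patient incidence.

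**AKI is not counted only when serious.** All treatment-emergent events are tabulated. The seriousness filter applies to the composite and the individual SAE counts. This also stands.

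**AKI is not the established harm of PCC.** The meta-analysis shows no increase, the sponsor's own matched cohort found similar adverse-event profiles, and Protocol 1.1 lists limitations of the second cohort with a signal, including possible salvage use of PCC. The accurate statement is that AKI is one named risk with conflicting evidence.

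**Reporting need not differ between arms.** Outcome assessors are blinded (Protocol 5.2) and staff search patient records for events (Protocol 7.4.2). The documents do not support a claim of differential reporting. They also do not name AKI as a surgery-expected event; listing it in the composite points the other way. What remains is an exclusion rule with no boundary.

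**Creatinine has its own weaknesses.** Sampling follows routine care and stops at discharge, and treating clinicians know the arm once the seal is broken. A maximum depends on how often it is measured. This stands, and the fix must show it.

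**Conclusion.** The point holds as a worthwhile, inexpensive improvement. AKI is a named safety and composite component without an objective definition, and no planned output gives the share of patients in each arm whose creatinine rose by a stated multiple of baseline. The reference-range displays detect such rises poorly: 29% to 63% under the assumptions above, with misses both within normal and from an already high baseline.

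The effect of incomplete reporting depends on rates that the documents do not give. If half the cases went unreported in both arms, the risk difference would halve and the risk-ratio interval would widen, by factors such as 1.97 to 2.82.

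A reader might infer that a creatinine definition buys an interval about 40% narrower. That is true only for the log odds ratio, under assumed rates and the same odds ratio for mild and serious AKI; for the risk difference the interval widens. At 50 per arm neither definition gives a powered comparison. The benefit is a rate that can be reproduced and carried into Phase 3.

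**What to change.** Add to SAP 4.7 a derived AKI variable for every patient in the SAF and ITT populations:

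- **Definition.** The ratio of maximum creatinine through POD-7 to baseline, with one prespecified cut and one sensitivity cut chosen by the sponsor. Include new dialysis where records or AE data show it, since no dialysis field is listed.
- **Baseline.** State whether it is the last preoperative value or the last value before first IMP (SAP 4.1.1), which may be an intraoperative sample. The choice changes every ratio.
- **Reporting.** By arm, give the risk difference and a ratio measure, each with a 95% CI, next to reported AKI events.
- **Sampling.** By arm, show the number of creatinine values per patient, and count and list patients without a later value as not assessable.

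The creatinine part costs one variable and one table, with no new tests. Some patients will not be assessable.

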### 3.1.3 Additional Endpoints

The following additional endpoints will be collected:

1. Duration of mechanical ventilation (measured as duration of ventilation and ventilator-free days) up to POD-28.
2. Duration of intensive care unit (ICU) stay up to POD-28.
3. Duration of hospitalization up to POD-28.
4. Mortality up to POD-28.
5. Compliance of transfusion practice with the study's hemostatic algorithm based on review of patient charts by 2 blinded adjudicators. This will include comparison of lowest hemoglobin concentration during the first 24 hours after the start of surgery.

## 3.2 Overall Study Design and Plan

This is a multicentre, randomized, active-control, pragmatic, Phase 2 pilot study in adult cardiac surgery patients. Two Canadian hospitals (Toronto General and Sunnybrook hospitals, Toronto) will participate and it is estimated that the study will take approximately 9 months to complete.

Approximately 120 bleeding adult cardiac surgical patients who require coagulation factor replacement after cardiac surgery, according to accepted clinical standards, will be included. Patients will be randomized to receive equivalent doses of either PCC (*Octaplex*) or FP when the blood bank receives the first order for coagulation factor replacement and deems it to be in accordance with accepted clinical standards. Patients will be treated according to their assigned group on the first and second times when coagulation factor replacement is ordered during the treatment period (up to 24 hours after randomization) [see flowchart on the next page]. For any additional doses (i.e., the third dose and thereafter), patients in both groups will receive FP (in 1 U increments at the discretion of the ordering physician). No other aspects of care will be modified.

**Figure 1. Study Flow**

[figure not shown]

\*PCC dose corresponds to a weight-based dosing range of 20–25 IU/kgIBW rounded up to nearest 500 IU increment, up to a maximum of 2000 IU per dose

†FP dose corresponds to a weight-based dosing range of 10–15 mL/kgIBW rounded up to the nearest 1 U increment, up to a maximum of 4 U per dose

‡FP in 1 U increments at the discretion of the ordering physician

PCC, prothrombin complex concentrate; FP, frozen plasma; IU, international units; RBC, red blood cell concentrate

### 3.3 Discussion of Study Design and Choice of Control Group

#### 3.3.1 Study Aims

This pilot study aims to select a clinically relevant primary efficacy endpoint for a phase 3 study, which will subsequently aim to determine if PCC is non-inferior or superior to FP in terms of the selected primary efficacy and safety endpoints in bleeding cardiac surgical patients.

#### 3.3.2 Dose Rationale

Each time coagulation factor replacement is ordered, patients will receive either *Octaplex* (1 dose = 1500 IU for IBW ≤ 60 kg or 2000 IU for IBW > 60 kg; based on 20–25 IU/kgIBW, rounded up to nearest 500 IU increment

on a standard dosing chart, up to a maximum of 2000 IU per dose) or FP (1 dose = 3 U for  $IBW \leq 60$  kg or 4 U for  $IBW > 60$  kg; based on 10–15 mL/kgIBW, rounded up to the nearest 1 U increment, up to a maximum of 4 U for each order) according to their group assignment. If an order for a second dose is received, the second dose of *Octaplex* or FP will be released and administered to patients according to the randomized group allocation as per the first dose. For any additional doses (i.e., the third dose and thereafter), patients in both groups will receive FP (in 1 U increments at the discretion of the ordering physician).

The doses of PCC and FP selected for the study represent current clinical practice at the study sites (choice currently decided by the cardiac anesthesiologist) and will only be given to patients in whom the therapies are clinically indicated as per the ordering physicians. There is an absence of a consensus of guidelines regarding PCC dosing in acquired coagulation factor deficiency; however, the dose of PCC is consistent with current clinical practice and is similar to doses used previously in other studies in a cardiac setting (4, 31, 59, 73). It is also equal to or lower than doses of PCC that have demonstrated a good safety and tolerability profile in other clinical settings (e.g., factor Xa inhibitor reversal in major bleeding (68, 69, 74) and trauma (70, 75).

### 3.3.3 Choice of Comparator

The trial will not include a placebo arm because delaying coagulation factor replacement in bleeding patients may expose them to the negative consequences of excessive blood loss, is not consistent with standard practice (76, 77), and would withhold an effective treatment from patients and thus be unethical. Moreover, the question being addressed does not meet any of Freedman's five conditions that would justify the use of a placebo control, which are: 1) no standard treatment exists; 2) standard treatment is not better than placebo; 3) standard treatment is a placebo or no treatment; 4) new evidence has shown uncertainty of the risk-benefit profile of the standard treatment; and 5) effective treatment is not readily available due to cost or supply issues (77, 78).

### 3.3.4 External Validity

The definitive phase 3 study will be a pragmatic study performed in multiple hospitals with different characteristics. Moreover, patients will be recruited and randomized after the clinical team orders coagulation factor replacement and the only change to routine practice is dictating the choice of coagulation factor replacement amongst the two therapies that are currently available and used interchangeably. For these reasons, the phase 3 study will have good external validity.

### 3.3.5 Randomization and Baseline Differences

Given the size of this pilot study and random patient assignment stratified by centre, study groups should be reasonably balanced with respect to important clinical variables and this should allow selection of an appropriate endpoint for the confirmative Phase 3 study. The random allocation schedule will be prepared by a biostatistician not involved in the conduct of the trial, and neither the individual randomizing nor any of the health care providers will know which treatment will be assigned to the patient when coagulation factor replacement is ordered.

### 3.3.6 Recruitment and Informed Consent

This is a pragmatic trial that compares two coagulation factor replacement therapies that are currently within the standard of care for this procedure and poses no additional risks to patients and entails no additional interventions outside of normal clinical care. Moreover, due to the emergency nature of the condition being studied

(i.e., bleeding during or after surgery), the trial will include only patients who are incapable of providing informed consent at the time the therapy is needed and in whom delays in obtaining surrogate consent can be severely detrimental to their well-being. Thus, this study qualifies for alteration to consent requirement before randomization. However, we will obtain consent from patients or their surrogate after surgery. The alteration to the informed consent process meets the criteria of the Tri-council policy statement for the ethical conduct for research involving humans, as is outlined in **Section 10.3**.

